## Abstract

**Background:**

The progressive aging of the population has meant the increase in elderly patients requiring an urgent surgery. Older adults, especially those with frailty, have a higher risk for complications, functional and cognitive decline after urgent surgery. These patients have their functional and physiological reserve reduced which makes them more vulnerable to the effects of being bedridden. The consequences are at multiple levels emphasizing the functional loss or cognitive impairment, longer stays, mortality and institutionalization, delirium, poor quality of life and increased use of resources related to health.

We aim to determine whether postoperative physical rehabilitation can prevent functional and cognitive decline and modify the posterior trajectory.

**Methods/design:**

This study is a randomized clinical trial, simple blinded, conducted in the Department of Surgery of a tertiary public hospital in Navarra (Hospital Universitario de Navarra), Spain. Patients >  = 70 years old undergoing urgent abdominal surgery who meet inclusion criteria will be randomly assigned to the intervention or control group. The intervention will consist of a multicomponent physical training programme, which will include progressive and supervised endurance, resistance and balance training for 4 weeks, twice weekly sessions with a total of 8 sessions, and the group control will receive the usual care. The primary outcome measure is the change in functional (SPPB) and cognitive status (Mini-Mental State Examination) and the change of quality of life (EuroQol-5D-VAS) during the study period. The secondary outcomes are postoperative complications, length of stay, delirium, mortality, use of health resources, functional status (Barthel Index and handgrip strength tests), cost per quality-adjusted life year and mininutritional assessment. The data for both the intervention group and the control group will be obtained at four different times: the initial visit during hospital admission and at months 1, 3 and 6 months after hospital discharge.

**Discussion:**

If our hypothesis is correct, this project could show that individualized and progressive exercise programme provides effective therapy for improving the functional capacity and achieve a better functional, cognitive and quality of life recovery. This measure, without entailing a significant expense for the administration, probably has an important repercussion both in the short- and long-term recovery, improving care and functional parameters and could determine a lower subsequent need for health resources. To verify this, we will carry out a cost-effectiveness study.

The clinical impact of this trial can be significant if we help to modify the traditional management of the elderly patients from an illness model to a more person-centred and functionally oriented perspective. Moreover, the prescription of individualized exercise can be routinely included in the clinical practice of these patients.

**Trial registration:**

ClinicalTrials.gov Identifier: NCT05290532. Version 1. Registered on March 13, 2022.

**Supplementary Information:**

The online version contains supplementary material available at 10.1186/s13063-024-08406-0.

## Background

The population in developed countries is rapidly aging; the number of Americans aged 65 years or older was 43 million in 2012, and this number is expected to be more than doubled by 2060 [1]. The United Nations in its report “World Population Prospects 2019: Highlights” estimates that, in 2050, one in six people in the world will be over 65 years old (16%) [2]. Specifically in Spain, in 2050, people over 65 will represent more than 30% of the total population and octogenarians will exceed 4 million [3]. This rapid rate of population aging has been outpaced by an increase in number of older patients needing surgical intervention as a main modality of treatment [4–6].

There still exists lack of consensus about the definition of what age is considered the cutoff for geriatrics (65 vs 70 vs 75 years old), and there is consensus that patients should not be treated based on their age alone [7]. However, there is evidence that age-related psychophysiological changes and co-morbidities affect older people’s tolerance to surgery, becoming a major life event with the risk of permanent and definitive disabilities [8]. Frailty is a clinical syndrome defined by vulnerability and an increased risk of the individual to develop negative health-related events such as disability and/or mortality under external stressor factors such as surgery [9]. To identify older adults at high risk of numerous adverse outcomes, five criteria have been established weight loss, exhaustion, leisure-time activity, gait speed and grip strength [10].

Related to this, quality of life has become one of the main health goals of the twenty-first century. Older adults consistently indicate that maintaining independent function is their top priority, more than 70% of the elderly would not choose a treatment that would lead to severe functional impairment, even if we ensured their survival [11–14]. Hospital admission in these patients often leads to significant functional impairment; between 20 and 46% of patients have functional loss in one or more activities of daily life [11, 15–17]. Of these patients who present functional deterioration at discharge, recovery of the baseline situation is achieved in only 30% of them, most within the first month [18].

To reduce functional decline in older adults undergoing elective surgery, multimodal rehabilitation programmes ERAS (Enhanced Recovery After Surgery) have been designed. Several previous studies have included supervised exercises as multimodal rehabilitation; these programmes aim to promote postoperative recovery in elective surgery. They have subsequently been extrapolated to urgent surgery proving that once adapted they are effective [19–21].

Focusing on the elderly patient undergoing surgery, the functional recovery is severely affected in the subgroup of patients who have required urgent surgery and in those with post-surgical complication [16, 17, 22]. In urgent surgery patients, prehabilitation programme cannot be performed, although post-surgical rehabilitation is feasible. Rehabilitation based on physical exercise during admission in elderly patients after an acute process has shown an earlier recovery of their baseline functional status [23–28]. However, there are few recommendations for rehabilitation programmes including physical activity in older patients after urgent surgery.

We developed the first randomized clinical trial to assess the effectiveness of a rehabilitation programme based on physical exercise during the first month after surgery.

The main objective of this study is to analyze whether postoperative physical rehabilitation in a short period of time improves functional and cognitive recovery and long-term quality of life (6 months) in elderly adults undergoing urgent abdominal surgery.

## Methods/design

### Study design

This study is a parallel group, two-arm, superiority randomized trial with 1:1 allocation ratio, is monocentric and is conducted in the Department of Surgery of a tertiary public hospital in Navarra (Hospital Universitario de Navarra), Spain. Patients undergoing urgent abdominal surgery who meet inclusion criteria will be randomly assigned to the intervention or control group.

Patient recruitment will begin in 4 days after the surgical procedure, and these patients will be identified through the list of patients admitted to the hospital and assigned to the Department of General Surgery. Prior to randomization, the investigators will review the contraindications to participate in the exercise programme and will provide general information about the study. After signing an informed consent form, the subjects will be chosen randomly. 

Randomization will be performed by applying http://www.randomizer.org/. The doctor who decides the inclusion in the intervention or control group will not be the attending physician. Patients will be informed of the random inclusion in one of the groups.

The information in both groups is obtained in four different stages: the initial visit and at months 1, 3 and 6 after hospital discharge.

The protocol employs relevant standard protocol items for clinical trials according to the SPIRIT 2013 statement [29] and follows the CONSORT statement [30] for transparent reporting.

The trial is registered at ClinicalTrials.gov, identifier NCT05290532.

### Study participants and eligibility criteria

Individuals ≥ 70 years old admitted to the Department of General Surgery of the Hospital Universitario de Navarra after an urgent surgery between March 2022 and March 2025.

The inclusion criteria are (Fig. 1):Age 70 years and olderUndergoing urgent abdominal surgeryAble to ambulate, with or without personal / technical assistance or move unassisted in a wheelchairAble to communicate: English or SpanishBarthel Index > 60.Informed consent: must be capable and willing to provide consent.

**Fig. 1 Fig1:**
[figure not shown]
Inclusion and exclusión criteria, groups and follow-up

The exclusion criteria are (Fig. 1):Severe dementia (GDS 7)Unwillingness to either complete the study requirements or to be randomized into control or intervention groupUnstable cardiovascular disease or other unstable medical conditionMyocardial infarction in the past 3 monthsTerminal illnessChronic kidney disease: dialysisUpper or lower extremity fracture in the past 3 monthsEviscerationPatients transferred to a rehabilitation clinic prior to home discharge

If the patient throughout the study presents any of the exclusion criteria and wishes to leave the study, they will be removed from the study.

### Randomization and blinding

The study participants will be randomized into an intervention group and a control group following a simple randomization procedure with a 1:1 allocation through a computer system (www.randomizer.org). The doctor who decides the inclusion in the intervention or control group will not be the attending physician, and the assessment staff will be blinded to the participant randomization assignment. It will not be possible to conceal the group assignment from the staff involved in the training of the intervention group. Due to the nature of the study, patients may not be blinded as to the group to which they belong.

### Sample size and statistical analysis

Assuming a type I error of 0.05, a correlation between pre and post-intervention values of the Short Physical Performance Battery (SPPB) of *r* = 0.6 and a standard deviation for the SPPB of 2.5, the required sample size to detect with a power of 90% a minimum difference of 1 point between groups in the change of SPPB score is 87 patients per group [27]. Assuming losses of 20%, the final objective of the size of each group is 109 patients, and, consequently, a total sample size will be 218 subjects. For the estimation, an ANCOVA method for the analysis of the differences has been considered. The outcome variables will be analyzed using mixed models, without missing data imputation. If the proportions of missing data are very large (more than 40%) on important variables, then trial results will be considered as hypothesis-generating results.

Baseline values will be compared by group using descriptive statistics as mean and standard deviation or median and interquartile range for quantitative variables and frequencies and percentages for categorical ones. To determine the efficacy of the intervention in the quantitative variables, such as the SPPB, we will use ANCOVA models, using post-intervention value as dependent variable, group study as the principal effect and pre-intervention value as covariate. If relevant group differences were observed at baseline, we would adjust for these variables in the model. In the case of qualitative or categorized variables (such as whether an improvement of a given magnitude between pre and post-intervention has been achieved or not), comparisons between groups will be conducted with the chi-square test or Fisher’s test, and complemented with logistic regression if additional adjustment is needed.

The level of statistical significance will be 0.05. Data will be analyzed using an intention-to-treat approach and using SPSS and R statistical software.

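### Observed baseline imbalance, rather than a list fixed in advance, decides which covariates enter the efficacy model; the cost is a somewhat conservative test and forgone power, not inflated error

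*Protocol article*

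**What the plan says.** Under *Sample size and statistical analysis*, the protocol article models each quantitative outcome, with the SPPB as its example, by ANCOVA: the later value is regressed on study group and the earlier value. The next sentence is the rule at issue: "If relevant group differences were observed at baseline, we would adjust for these variables in the model". It is not described as a sensitivity analysis, so it governs the main efficacy model for the outcome that sized the trial. Categorised outcomes get a similar provision: logistic regression is added where further adjustment is thought necessary.

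The same section also says that outcomes will be analysed with mixed models. The covariate rule is attached to the ANCOVA.

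Under *Randomization and blinding*, patients are allocated "following a simple randomization procedure with a 1:1 allocation", and no stratification factor is mentioned. The test level is stated plainly: "The level of statistical significance will be 0.05".

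**The concern.** When allocation is random, a difference between the arms at baseline is a chance event. It says nothing about whether the variable predicts the outcome, and a well-balanced variable may predict it strongly. Choosing covariates by imbalance therefore selects on the wrong property. Two repetitions of this trial could end with different models for the same question.

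The rule also has a statistical cost. When a prognostic covariate happens to be balanced and is left out, the treatment estimate is in truth more precise than its standard error says, because the covariate's contribution stays in the residual variance. Adjusting only in the unbalanced cases leaves that overstatement in all the others. The expected result is a test below its nominal size, and a loss of the precision that the same covariates would bring if always included.

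**Working it through.** **Inputs from the article** (*Sample size and statistical analysis*): type I error 0.05, taken as two-sided because sidedness is not stated; pre-post correlation 0.6; "a standard deviation for the SPPB of 2.5"; a 1-point difference; 90% power; 87 per group.

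**The plan's own figure.** The ANCOVA residual SD is 2.5 × √(1 − 0.6²) = 2.0. Then n = 2 × 2.0² × (1.960 + 1.282)² / 1² = 84.06, so 85 per group. Noncentral-t power is 90.0% at 85 and 90.6% at 87. The stated 87 is thus reproduced to within two patients. The alternatives do not fit: change score 106, post score alone 132, one-sided ANCOVA 69. For losses, 87 / 0.80 = 108.75, which agrees with "Assuming losses of 20%, the final objective of the size of each group is 109 patients". The sample size is sound and is not in question.

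**Assumptions the article does not supply.** There are one or five further baseline covariates, independent of baseline SPPB, together explaining 10%, 30% or 50% of the residual variance (50% with five covariates only). A covariate enters if its baseline difference has p < 0.05, or a standardised difference above 0.1, or above 0.2. There is one post-intervention value, 87 per group, and baseline SPPB is always in the model. Each scenario used 20,000 runs with no effect (Monte Carlo standard error √(0.05 × 0.95 / 20,000) = 0.15 points) and 8,000 runs with a 1-point effect.

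**Results** (%, range over triggers and number of covariates):

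| Residual variance explained | Size, rule | Size, fixed list | Power, baseline value only | Power, rule | Power, fixed list | Points given up by rule against fixed list |
|---|---|---|---|---|---|---|
| 10% | 4.3–4.9 | 4.7–5.2 | 90.1–90.9 | 90.9–91.9 | 92.0–93.0 | 0.9–2.1 |
| 30% | 3.3–4.4 | 4.8–5.2 | 90.1–90.8 | 91.1–95.6 | 96.9–97.6 | 1.9–5.8 |
| 50% | 2.5–3.5 | 4.8–5.1 | 90.2–90.5 | 92.1–98.1 | 99.4–99.6 | 1.5–7.3 |

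The fixed-list column can be checked by hand. With 30% explained, the residual SD is 2.0 × √0.7 = 1.673, the standard error is 1.673 × √(2/87) = 0.254, and power is about Φ(1/0.254 − 1.96) = Φ(1.98) = 97.6%.

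**How often the rule fires.** The standard error of a standardised difference is √(2/87) = 0.152, so the chance that one covariate exceeds 0.2 is 0.187, and with five it is 1 − 0.813⁵ = 0.645. In the simulations, one covariate triggered in about 5% (p < 0.05), 19% (above 0.2) or 51% (above 0.1) of trials; five covariates did so in 23%, 65% or 97%. A baseline table of all 109 per group would trigger less: √(2/109) = 0.135, chance 0.140 each, and 1 − 0.860⁵ = 0.53 for five.

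**If the cut-off were picked after seeing outcomes.** Counting a trial as positive if the baseline-only model, or the model at any cut-off from 0.1 to 0.3, is significant gives a size of 6.3% (one covariate, 30%), 6.6% (five, 10%) and 7.3% (five, 30%), from 15,000 null runs each.

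**The case against.** The strongest reply is that the rule does little harm. Applied as written it errs on the safe side, and it has power equal to or slightly above ANCOVA on the baseline value alone, which already meets the 90% target. The loss exists only against a better model, and at 10% of residual variance it is 1 to 2 points. All of this stands.

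A reader might infer that the rule inflates the false-positive rate. The article does not support that. Its trigger is the baseline comparison, which is described as descriptive, and nothing permits choosing between models by their p values. The 6.3% to 7.3% figures describe a misuse that the wording does not exclude, not a stated plan.

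A reader might also infer that adjustment is nearly certain to be triggered because randomisation is simple. That is unsupported too: the frequency depends on a number of candidates and a threshold that are not in the article, and blocking on arm size alone would leave chance imbalance in covariates almost unchanged.

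Finally, a definition of *relevant* and a list of candidates may stand in a full protocol or analysis plan that is not shown. Their absence is not the finding. *Relevant* might even mean prognostically relevant, which would soften the criticism. But the article states affirmatively that an observed difference triggers adjustment, and a plan that followed this would still select covariates by chance imbalance, whatever threshold it set.

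**Conclusion.** The point holds in a limited form. The stated rule makes the covariates of the efficacy model depend on chance imbalance and on judgement. The size and power costs in the table rest on the assumed prognostic strength, number of covariates and trigger, and on a single follow-up value; a mixed model over all visits was not simulated. They are modest and do not undermine the trial's validity or its sample size. The sentence is still worth changing, because a fixed list keeps the test at its nominal size within simulation error, removes the discretion and gives at least as much power in every scenario examined.

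**What to change.** Replace the sentence with a covariate list fixed before any comparative data are examined and used whatever balance is observed. It would hold the baseline value of the outcome plus a few baseline variables judged prognostic in advance. Age and type of surgery are natural examples. The section *Methods for further analysis* names them as subgroup factors, so their prognostic value needs its own justification. Comorbidity could be added if a baseline measure is recorded; none appears among the outcome measures or in the assessment table. Hospital stay, also a subgroup factor, should stay off the list because it is a secondary outcome.

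Use the same list in the ANCOVA or mixed models and in the logistic models; in the latter the odds ratio itself changes meaning with the covariate set. Keep the model with the baseline value alone, and any imbalance-driven adjustment, as sensitivity analyses.

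The cost is one sentence and a few degrees of freedom: the baseline-only ANCOVA has 174 − 3 = 171 residual degrees of freedom, and five further terms would leave 166. If the chosen covariates turn out weakly prognostic, the gain in power will be small.

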### Outcome measures

#### Primary outcome

The primary outcome measure is the change in functional and cognitive status and the change of quality of life during the study period. The functional capacity of patients will be evaluated by the Short Physical Performance Battery (SPPB) (Annex 1), which combines balance, gait ability and leg strength using a single tool. The total score will range from 0 (worst) to 12 points (best). The SPPB test has been shown to be a valid instrument for screening frailty and predicting disability, institutionalization and mortality. The magnitude of meaningful change was a one-point change in the score which has clinical relevance. If the total score is less than 10, it indicates frailty and a high risk of disability and falls.

The capacity will be assessed with the Mini-Mental State Examination (MMSE) (Annex 2). This examination is composed of seven categories designed to assess specific cognitive functions: orientation to time (5 points), orientation to place (5 points), registration of three words (3 points), attention and calculation (5 points), recalling the three words (3 points), language (8 points) and constructive visual capacity (1 point).

The MMSE score ranges from zero to 30 points, and lower values indicate possible cognitive deficit. Values from 27 to 30 denote preserved cognitive functions; from 24 to 26, changes that do not suggest deficit; from 20 to 23, changes that suggest cognitive deficit. Scores from 20 to 26 represent mild cognition impairments; between 11 and 20, moderate cognition impairment; and scores under 10 represent severe cognition impairments.

Changes in quality of life will be assessed by EuroQol-5D-VAS (Annex 3). This is a generic health status questionnaire, consisting of five dimensions (mobility, self-care, usual activities, pain/ discomfort, anxiety/depression) including three responses. It also includes a visual analogue scale for recording an individual’s rating of their current health-related quality of life (scale 0 to 100).

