#### Secondary outcome measure

Postoperative complications: Clavien Dindo (Annex 4) and Comprehensive Complication Index (Annex 5)Length of stayDelirium: Confusion Assessment Method (CAM) (Annex 6)Mortality: number of days alive after admission to the hospitalUse of health resources: new admission to the hospital, admission to nursing homes and visits to the general practitionerFunctional status: Barthel index (Annex 7)Cost per quality-adjusted life year: both direct and indirect study participant costsMininutritional Assessment short form (MNA) (Annex 8)Handgrip strength test

Surgeons and physiotherapists will help participants to fill in the questionnaires. The information in both groups is obtained in a face-to-face consultation in four different stages: the initial visit and at months 1, 3 and 6 after hospital discharge. The questionnaires and tests are easy to perform, and the studio staff is qualified to perform them in a homogeneous way. The scales that we used to evaluate functional capacity [32, 33], mental state [34], quality of life [35] and nutritional status [36] have been validated for use in Spain.

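### The only analysis rule that fits the ordered Clavien-Dindo grade is chi-square/Fisher, which on the full grade table ignores the ordering and gives no direction of effect

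*Protocol article*

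**What the plan says.** All references are to the Protocol article.

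- **Sample size and statistical analysis, quantitative outcomes.** These are compared by ANCOVA, with the post-intervention value as response and the pre-intervention value as covariate.
- **Same section, categorical outcomes.** The scope is given as "In the case of qualitative or categorized variables (such as whether an improvement of a given magnitude between pre and post-intervention has been achieved or" (the bracket closes with the negative, so the example is a yes/no variable). The rule for such variables is that "comparisons between groups will be conducted with the chi-square test or Fisher’s test, and complemented with logistic regression if additional adjustment is needed".
- **Same section, general sentence.** "The outcome variables will be analyzed using mixed models, without missing data imputation". No model for ordered categories is named there or elsewhere in the section.
- **Secondary outcome measure.** The list begins "Postoperative complications: Clavien Dindo (Annex 4) and Comprehensive Complication Index (Annex 5"). The assessment table places both during admission and at 1 month.
- **Significance.** "The level of statistical significance will be 0.05".

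**The concern.** The section sorts outcomes into two kinds, quantitative and categorical. An ordered grade is neither a measurement suited to ANCOVA nor a set of unordered labels, and the wording sends it to the second kind.

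Pearson's chi-square and Fisher's exact test give the same answer however the grade columns are arranged. If exercise moved patients towards milder complications throughout the scale, the evidence for that single directional shift would be spread over as many degrees of freedom as there are grades minus one. Two things are lost:

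- **Power**, against a test that uses the order.
- **Interpretation.** A significant result on a table with many columns says the arms differ, but not whether complications were milder or worse with exercise. It also supplies no single effect estimate.

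**Working it through.** **1. The plan's own sample size.** The section gives alpha 0.05, power 90%, a pre-post correlation of 0.6, "and a standard deviation for the SPPB of 2.5", and concludes that the number needed for "a minimum difference of 1 point between groups in the change of SPPB score is 87 patients per group". Sidedness is not stated; two-sided is assumed.

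- ANCOVA residual SD = 2.5 × √(1 − 0.6²) = 2.0.
- n per group = 2 × 2.0² × (1.960 + 1.282)² / 1² = 84.06, so 85. The stated 87 is within two patients of this and gives power of about 0.91.
- Allowing for 20% losses: 87 / 0.80 = 108.75, so 109, as stated.

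The figures reproduce, but they concern the SPPB only. No power is stated for Clavien-Dindo. The values 87 and 109 are used below only as plausible numbers analysed.

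**2. Cost of ignoring order, in theory.** Suppose a 1-df ordinal test has 80% power. Its noncentrality is (1.960 + 0.842)² = 7.85. Refer the same noncentrality to a chi-square with k − 1 degrees of freedom for k grades:

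| Grades | df | Power | Loss (points) |
|---|---|---|---|
| 2 | 1 | 0.800 | 0 |
| 4 | 3 | 0.645 | 15.5 |
| 6 | 5 | 0.555 | 24.5 |
| 8 | 7 | 0.493 | 30.7 |

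**3. Simulation with assumed grade distributions.** Grades in each arm are multinomial, and the exercise arm is shifted by a common cumulative odds ratio (OR) towards milder grades. Pearson chi-square on the full table is compared with the tie-corrected Wilcoxon test, two-sided 0.05. One assumed control distribution is: none 40%, I 15%, II 25%, III 10%, IV 5%, V 5%. At OR 2 the share with no complication has odds 2 × 0.40/0.60 = 1.33, which is 57%. With 20,000 simulated trials per row:

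| n per group | OR | Chi-square, full table | Wilcoxon | Any complication, yes/no | Grade III or higher, yes/no |
|---|---|---|---|---|---|
| 87 | 1.5 | 0.16 | 0.31 | 0.28 | 0.17 |
| 87 | 2 | 0.41 | 0.69 | 0.64 | 0.36 |
| 87 | 3 | 0.84 | 0.97 | 0.95 | 0.67 |
| 109 | 2 | 0.52 | 0.79 | 0.72 | 0.45 |
| 109 | 3 | 0.92 | 0.99 | 0.98 | 0.77 |

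Under no effect (OR 1) the full-table chi-square and the Wilcoxon test both reject in about 5% of trials, so both are valid.

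**4. Range over other assumptions.**

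- Six levels, three other distributions, OR 2: chi-square 0.32–0.45 against Wilcoxon 0.60–0.72 at n = 87, and 0.40–0.56 against 0.68–0.81 at n = 109.
- Eight levels, OR 2: 0.35 against 0.68 at n = 87, and 0.44 against 0.79 at n = 109. The last is the largest loss, 35 points.
- Four levels, OR 2, n = 87: 0.46 against 0.64.
- Smallest full-table loss: six levels, OR 3, n = 109, 0.94 against 0.99, about 5 points.
- Cut to any complication: losses from about 0 (0.286 against 0.290) to about 13 (0.492 against 0.624).

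Most full-table losses lie between 14 and 30 points.

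**The case against.** The strongest reply is that the article never names Clavien-Dindo under the chi-square rule. The one example given there is binary, the general mixed-model sentence competes with it, and the words logistic regression do not exclude an ordinal version. The grade might also be dichotomised, in which case the test itself ignores no order. The article is condensed, and an analysis plan that is not shown may settle the matter. Both tests hold their type I error, so this is a question of efficiency.

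Much of this stands. That Clavien-Dindo would be tested as a full unordered table is an inference, not a statement in the document. Against it, the binary case is offered only as an illustration, the mixed-model sentence names no model for ordered data, and logistic regression is reserved for when adjustment is needed. The article does not merely leave the choice open: it states a rule, and that rule is the only one that fits the grade. Dichotomising is not a safe escape without a stated cut-point. In the table above, a cut at any complication costs little, while a cut at grade III or higher does worse than the full-table chi-square at most of the effect sizes shown.

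Three stronger readings are tempting and are not supported:

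- **A fixed loss of 16 to 34 points for this trial.** Every input behind such a figure (grade distribution, number of levels, odds ratio) is assumed. It describes mid-range effects on the full scale only.
- **The same fault in the EuroQol-5D dimensions.** The article describes them as "consisting of five dimensions (mobility, self-care, usual activities, pain/ discomfort, anxiety/depression) including three responses", but nowhere plans to compare single dimensions between arms. A three-level item would have 2 degrees of freedom, with a loss of about 9 points in the setting of step 2 (0.71 against 0.80).
- **Severity effects going unseen altogether.** The Comprehensive Complication Index is listed beside Clavien-Dindo and, handled as a numeric score, retains severity information. It does not repair the Clavien-Dindo comparison itself.

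**Conclusion.** The point holds in a limited form. The stated rule that fits the Clavien-Dindo grade is a poor choice for an ordered scale, because on the full table it discards the ordering and gives no direction of effect. The size is conditional: roughly 5 to 35 points of power (mostly 14 to 30) on the full table, and about 0 to 13 points if cut to any complication. This rests on assumed grade distributions with four to eight levels, a proportional-odds shift with OR about 1.5 to 3, two-sided 0.05, and 87 to 109 patients per group. The consequence is confined to one secondary outcome. The SPPB sample size and the validity of the tests are not in question. It is worth correcting because correction is nearly free, not because the trial's main conclusions depend on it.

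**What to change.** In Sample size and statistical analysis, restrict chi-square and Fisher's test to binary or unordered variables. Add that the highest Clavien-Dindo grade will be compared between arms with a proportional-odds (ordinal logistic) model, reporting the common odds ratio with its 95% confidence interval, or with the Wilcoxon rank-sum test. If a dichotomy is preferred, fix the cut-point before the data are seen.

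The cost is one sentence. SPSS and R, already named, can do either analysis, and no extra data or patients are needed. The only added work is checking the proportional-odds assumption.
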